## Trial Summary

Breast cancer (BC) is a common malignant disease in women worldwide. Most women with BC undergo complex treatment regimens including surgery to remove the tumour and affected lymph nodes, as well as chemotherapy, radiation and/or endocrine therapy. Treatment for BC results in many side effects that compromise physical and emotional health. The time-consuming demands of the treatment itself together with the treatment side effects result in time away from work and/or other meaningful life activities.

There is emerging evidence that exercise interventions undertaken during or after completion of cancer treatment optimises physical function, emotional health and reduces fatigue. Australian and international cancer organisations now advocate that individuals should participate in regular exercise while undergoing their BC treatment. Although usual care pathways at the Royal Perth Hospital (RPH) Breast Clinic physiotherapy service involves education of the importance of exercise, it is possible that a more structured, individualised and supervised approach to exercise prescription would produce greater benefit in this population of patients, including improved physical activity maintenance after completion of the program.

Our study will explore the effect of an experimental exercise program (known as the *SMART* program; [Self-determined Monitored Adaptable Rehabilitation with Telehealth support]) in adults accessing the Breast Clinic at RPH. The experimental program will be tailored to each person and provide supervised exercise sessions either in person or via telehealth in addition to regular behaviour change interventions. The primary outcome will be disease-specific health-related quality of life. Secondary outcomes will include peripheral muscle strength, exercise tolerance, fatigue, chemotherapy completion rates, healthcare utilisation, psychological determinants of behaviour change and mood.

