### 3 Trial Aims / Objectives / Hypotheses

For all research questions, the study population refers to adults with newly diagnosed with breast cancer who are undergoing treatment through the Breast Clinic at RPH.

Primary research questions:

- 1) Does the SMART program, compared with usual care, change health-related quality of life (primary outcome) measured 16-weeks and 12-months following randomisation?
- 2) Does the SMART program, compared with usual care, change peripheral muscle strength, muscle mass, exercise tolerance, exercise adherence and chemotherapy completion rates (secondary outcomes) measured 16 weeks following randomisation?

Secondary research questions:

- 1) Do factors such as adherence, treatment pathway and cancer stage moderate the magnitude of any change in primary or secondary outcomes? (i.e. moderator analysis)
- 2) What is the health care utilisation, absenteeism and presenteeism over the 12 months following randomisation? (descriptive analyses only, to guide patient expectations in regarding these outcomes)

- 3) Does performance on tests of peripheral muscle force-generating capacity and exercise tolerance, change with test repetition (i.e. is there a learning effect)? (can be answered by Honours students enrolled in the BSc physiotherapy at Curtin University)
- 4) What is the minimal detectable difference in health-related quality of life and exercise tolerance? (can be answered by Honours students enrolled in the BSc physiotherapy at Curtin University)
- 5) Do psychological determinants of behavioural change, such as capability, opportunity, and motivation affect adherence to the SMART program and physical activity maintenance?
- 6) Does the SMART program improve mood, and does mood influence adherence to the program and physical activity maintenance?

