**Exercise tolerance** will be measured as the six-minute walk test (Schmidt 2013). This test will be performed according to standard guidelines (Schmidt 2013). The outcome measured is the distance walked in 6 minutes (6MWD). Each participant will perform the test twice and the longest 6MWD will be recorded as the test result.

**Muscle mass** and body composition will be measured via bioimpedance spectroscopy. This is a non-invasive measure of body composition performed using the SOZO analyser (Impedimed, Brisbane, Queensland). The test takes under a minute, with the participant clothed and standing on the testing platform. The SOZO device is already used in standard care in patient with BC to identify the presence of lymphoedema. This device applies 256 discrete current frequencies through the body, which provides estimates of tissue composition (skeletal muscle mass, fat mass, fat free mass), fluid variables (total body water, extracellular fluid and intracellular fluid), and a metabolic report (cell health, basal metabolic rate and active tissue mass) (Kyle, et al, 2004; Grisbrook, et al, 2015).

**Chemotherapy completion rates** will be extracted from medical records and recorded as a mean relative dose intensity (RDI), which records the actual chemotherapy medication dose intensity as a fraction of the original planned dose intensity, accounting for both the dose and the number of weeks in the chemotherapy cycle (Longo 1991). Any dose adjustments or dose delays will be obtained from the medical records and/or the treating oncologist and the percent of participants requiring dose adjustments or delay will be recorded.

**Psychological determinants of behaviour change** will be measured using; (i) the Capability, Opportunity, Motivation – Behaviour (COM-B; Michie et al. 2011) model factors, (ii) impairment in functioning, (iii) intention, (iv) self-efficacy, (v) habit. These are described below:

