## 9 Data Management, Statistical Analysis and Record Keeping

## Statistics and Interim Analysis

*The primary research questions for this study are:*

- Does the SMART program, compared with usual care, change health-related quality of life (primary outcome) measured 16-weeks and 12-months following randomisation?

AND

- Does the SMART program, compared with usual care, change peripheral muscle strength, muscle mass, exercise tolerance, exercise adherence and chemotherapy completion rates (secondary outcomes) measured 16 weeks following randomisation?

The analyses for this research question will be performed according to the intention to treat principle. For the primary outcome, health-related quality of life, with 4 assessment points, linear models will be used to account for repeated measures with participant ID entered as a random effect. The primary time point of interest will be the end of the intervention phase. Group, time and group by time will be analysed as fixed effects and the baseline measure will be entered as a covariate to adjust for random baseline differences. Between group difference for the dependent outcome of chemotherapy completion (yes/no) will be analysed using logistic regression. Between group differences for the remaining secondary measures (peripheral muscle force-generating capacity, muscle mass, exercise tolerance) will be examined using linear regression with the corresponding baseline measure used as a covariate. Data transformations or alternative models (such as gamma distribution) will be considered if there is poor model fit.

Missing data will be examined and multiple imputations investigated (assuming they are missing at random). Models will be adjusted for covariates, randomisation variables and confounders such as age. Estimates of the effects will be reported with their corresponding 95% confidence intervals.

*The first secondary research question is:*

- Do factors such as adherence, treatment pathway and cancer stage moderate the magnitude of any change in primary or secondary outcomes? (i.e. moderator analysis)

To understand any moderator effects, the listed covariates will be entered into a multivariable model using the outcomes listed above. In addition, adherence will be examined to see if it mediates the relationship with the outcomes, by calculating the indirect through the use of partial coefficients.

*The second secondary research question is:*

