- What is the health care utilisation, absenteeism and presenteeism over the 12 months following randomisation?

This is an exploratory question and data will be described using mean and standard deviation.

*The third secondary research question is:*

- Does performance on tests of peripheral muscle force-generating capacity and exercise tolerance, change with test repetition (i.e. is there a learning effect)?

This will be assessed using one-way repeated measures analysis of variance (ANOVA). That is, for each participant, data collected over consecutive trials (5 attempts for each measure of muscle force and 2 attempts for the 6MWT) compared to explore if there is an effect of test repetition on these outcomes.

*The fourth secondary research question is:*

What is the minimal detectable difference in health-related quality of life and exercise tolerance?

This will be assessed using anchor-based approach via a Receiver Operating Characteristic curve. This curve will determine the optimal operating point to discriminate between participants who rate themselves as changed vs unchanged at the end of the SMART program.

*The fifth secondary research question is:*

Do psychological determinants of behavioural change, such as capability, opportunity, and motivation affect adherence to the SMART program and physical activity maintenance?

This will be assessed using correlations and a Multiple Regression Analysis of the data from psychological determinant measures (COM-B factors, impairment in functioning, intention, self-efficacy, habit, and mood) across all time-points for each participant. Data from the exit interviews will also be analysed using qualitative methods (such as thematic analysis) to explore participants' reasons for engagement (or lack of engagement).

*The sixth secondary research question is:*

Does the SMART program improve mood, and does mood influence adherence to the program and physical activity maintenance?

This will be assessed using correlations between mood data from the PANAS (across all timepoints) and physical activity engagement.

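### Psychological determinants and mood are declared secondary outcomes, but the protocol specifies no SMART-versus-control comparison for either

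*Protocol*

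**What the plan says.** **Declared status.** The Trial Summary states: "Secondary outcomes will include peripheral muscle strength, exercise tolerance, fatigue, chemotherapy completion rates, healthcare utilisation, psychological determinants of behaviour change and mood". Section 7, under the Secondary Outcomes heading, repeats the determinants as COM-B factors followed by "ii) impairment in functioning, (iii) intention, (iv) self-efficacy, (v) habit", and lists mood (PANAS) separately.

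**Schedule.** The timing table in Section 7 marks COM, WSAS, intention, BTSES, HTQ, SRBAI and PANAS at baseline, mid-way, end of intervention and 12 months. It makes no distinction by arm.

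**Questions.** Primary question 2 (Section 3) asks whether SMART, compared with usual care, will "change peripheral muscle strength, muscle mass, exercise tolerance, exercise adherence and chemotherapy completion rates (secondary outcomes) measured 16 weeks following randomisation". Determinants and mood are not in that list. Secondary question 5 runs the other way: "Do psychological determinants of behavioural change, such as capability, opportunity, and motivation affect adherence to the SMART program and physical activity maintenance". Secondary question 6 asks both whether SMART improves mood and whether mood influences adherence and maintenance.

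**Analyses (Section 9, Statistics and Interim Analysis).** Quality of life gets a repeated-measures model and chemotherapy completion a logistic regression. For the rest: "Between group differences for the remaining secondary measures (peripheral muscle force-generating capacity, muscle mass, exercise tolerance) will be examined using linear regression". On question 5: "This will be assessed using correlations and a Multiple Regression Analysis of the data from psychological determinant measures", taken "across all time-points for each participant". On question 6, only correlations between PANAS and physical activity are planned.

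**Healthcare utilisation.** It is in the Trial Summary list of secondary outcomes. Section 7 places it under Other Variables, and Section 3 limits it to "descriptive analyses only, to guide patient expectations in regarding these outcomes".

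**The concern.** A secondary outcome of a randomised trial is normally something on which the arms are compared. Here one family of declared secondary outcomes is measured four times in all participants and then used only to explain adherence and activity. For mood, the protocol asks an effect question and plans an analysis that cannot answer it.

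Two things are at stake. The first is interpretation. SMART includes explicit behaviour-change components (goal setting, action planning, problem solving, habit formation, coaching). If quality of life shows no difference, it would help to know whether intention or exercise habit moved at all. A link between determinants and adherence does not say, because people who adhere may differ in many other ways. The second is reporting. Declared outcomes without a stated comparison may go unreported as outcomes, or may be compared only once the data have been seen.

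**Working it through.** The point is structural, so the main check is to trace each item from declaration to question to analysis.

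| Item | Declared as | Question asked | Planned analysis | Arm comparison stated? |
|---|---|---|---|---|
| Muscle force, muscle mass, exercise tolerance | Secondary outcomes | SMART vs usual care (primary question 2) | Baseline-adjusted linear regression | Yes |
| Chemotherapy completion | Secondary outcome | SMART vs usual care (primary question 2) | Logistic regression | Yes |
| COM, WSAS, intention, BTSES, HTQ, SRBAI | Secondary outcomes | Do they affect adherence and maintenance? (question 5) | Correlations, multiple regression, interview themes | No |
| PANAS mood | Secondary outcome | Does SMART improve it? Does it influence adherence? (question 6) | Correlations with activity; also a predictor under question 5 | No |
| Healthcare utilisation | Secondary outcome in the Trial Summary; other variable in Section 7 | Descriptive (question 2) | Mean and standard deviation | No, by design |

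**Could the planned analyses still give an arm effect?**
- The question 5 regression has no stated group term, and the determinants are its predictors. For adherence to SMART itself, only the SMART arm can supply the response, so control-arm determinant scores have no role there.
- A correlation between mood and activity can be strong in both arms while mean mood is identical between them. It can address the second half of question 6, but not the first.
- The mediation analysis in Section 9 uses adherence as the mediator, not the determinants.

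**Scope.** The four-time-point schedule holds for the six determinant instruments and PANAS. The Brief Self-Control Scale is described in Section 7 but has no row in the timing table, so it is not counted.

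**Would an added comparison be feasible at the planned size?** Inputs from the Sample Size section: difference 8, SD 20.52, α = 0.05 (two-sided assumed, since this reproduces the stated number), power 0.8, 20% drop-out.
- Reproducing the plan: n per arm = 2 × (1.96 + 0.84)² × (20.52/8)² = 2 × 7.84 × 6.579 = 103.2, rounded up to 104. With drop-out, 104/0.8 = 130. Both match.
- Detectable standardised difference with 104 per arm, unadjusted: 2.80 × √(2/104) = 0.388 (0.390 by the t-test), so about 0.39 SD.
- With baseline adjustment, multiply by √(1 − r²), where r is the baseline-to-follow-up correlation. The protocol gives no r for these scales, so it is assumed: r = 0.3 gives 0.388 × 0.954 = 0.37; r = 0.5 gives 0.388 × 0.866 = 0.34; r = 0.7 gives 0.388 × 0.714 = 0.28 SD.

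These figures show feasibility only. They do not measure the defect, and no figure stated in the protocol changes. They also assume 104 evaluable per arm, which recruitment secures for week 16 but not for 12 months.

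**The case against.** The strongest reply is that the protocol promises a separate statistical analysis plan, and models for secondary questionnaires are commonly left to it. This stands in part. A reader might infer that the trial will never test these effects or has discarded them. The document does not support that: the data are scheduled in all participants, and the plan not shown could add the comparison. The supportable statement is that this protocol specifies none. It is still more than omitted detail, because the protocol itself sets question 5 in the predictor direction and names the measures to be compared.

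Second, question 5 and its analysis agree with each other, so the mismatch may be one of labels. That is fair for the determinants, and relabelling is a legitimate cure. It does not work for mood, where the stated question itself needs a comparison.

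Third, the list of remaining measures is loosely drafted: it also leaves out exercise adherence, which primary question 2 names. Omission from it is therefore weak evidence of deliberate exclusion. But the determinants and mood are absent from primary question 2 as well.

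Fourth, a reader might infer that SMART is built to change these determinants. The stated target behaviour is exercise volume. Habit formation and action planning are named techniques, but self-efficacy is not named in the intervention description, HTQ measures a general tendency, and WSAS measures impairment. The case is strongest for SRBAI and intention.

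Fifth, a reader might take these contrasts as the only unconfounded evidence on how SMART works. Exercise adherence is also named for randomised comparison, so they are not.

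**Conclusion.** The point holds as an internal mismatch. Six determinant instruments carry the label of secondary outcome with no SMART-versus-control comparison specified. Mood has the same gap in plainer form, since its own question asks for an effect. The conclusion rests on the protocol text alone and would be met if the unseen analysis plan adds the comparisons, though the protocol wording would then still need to be aligned.

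The consequence is moderate. The primary endpoint, its model and the sample size are untouched. What is lost, if the text is followed, is the randomised estimate for declared outcomes that the trial is large enough to give with useful precision (about 0.39 SD detectable unadjusted).

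Healthcare utilisation is a labelling matter only. A reader might infer that it too should be compared between arms, but the documents do not support that. It is descriptive by design, and Section 7 collects it at weekly sessions in SMART and by monthly calls in controls. An arm difference would carry unequal ascertainment.

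**What to change.** - In Section 9, add intention, SRBAI, BTSES, HTQ, WSAS and PANAS to the between-group analyses. Use the baseline-adjusted repeated-measures model already planned for quality of life, with an alternative where fit is poor, for example for intention, which has one item per behaviour.
- Report the SMART-minus-control difference at 16 weeks and 12 months with 95% confidence intervals, labelled non-confirmatory.
- Keep the question 5 and 6 correlations and regression as exploratory analyses.
- In the Trial Summary and Section 7, relabel any determinant not compared between arms as a predictor or exploratory variable. COM is the natural case: it is worded around achieving weekly exercise goals, which controls are not described as setting.
- Remove healthcare utilisation from the secondary outcomes in the Trial Summary.

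**Cost.** Protocol wording and some extra model runs, with no new data collection. The downside is more secondary estimates: 6 instruments × 2 time points = 12, or 8 × 2 = 16 if the two intention items and positive and negative mood are each kept separate. The non-confirmatory label is there for that reason.

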## 2 Rationale / Background

### Background summary

Breast cancer is a common disease, affecting 1 in 8 women over the course of their life (Cancer Australia 2023). In 2020, the worldwide incidence of BC was 2.26 million (Ferlay et al., 2020). Fortunately, survival rates from BC have improved dramatically such that currently, 9 out of 10 women remain in remission at 5 years following initial diagnosis (Giaquinto et al., 2022). Treatment for BC often includes surgical excision of the tumour and affected lymph nodes, chemotherapy, endocrine therapy and/or radiotherapy. Side effects of BC treatments include but are not limited to loss of skeletal muscle mass, reduced cardiovascular fitness, fatigue, pain, depressive symptoms and gastrointestinal symptoms (Bland 2019, Collins 2018, Feliciano 2017, Mijwel 2018). These side effects can persist for many years and serve to reduce health-related quality of life and physical function (Brown 2012). Addressing quality of life following treatment is of paramount importance, particularly with reports of

worsening quality of life 2-years after diagnosis (Ferreira 2019). Implementation of therapies and/or strategies to address these sequelae is urgently needed.

Encouragement to exercise has become part of usual care during and following completion of BC treatment. Data from several systematic reviews investigating the effects of exercise demonstrate positive effects on overall health-related quality of life (Mishra 2012; Zhang 2019), pain (Plinsinga 2022), fatigue (Meneses- Echavez 2015), physical function (Ficarra 2021) and mood (Salam 2022). Further, exercise interventions have been shown to reduce declines in physical fitness (Ficarra 2021) and improve chemotherapy completion rates (van Waart 2015). Importantly, exercise post-diagnosis significantly reduces BC-related mortality (Salam 2022). Despite this growing body of literature, effect sizes are modest and wide confidence intervals published across systematic reviews challenge our confidence in that effects will be clinically meaningful. This highlights the need for ongoing research to optimize outcomes from exercise interventions.

Nevertheless, National and International organisations e.g., the Clinical Oncology Society of Australia (COSA) routinely recommend that following any cancer diagnosis, individuals should complete at least 150 minutes per week of moderate intensity aerobic exercise or 75 minutes per week of vigorous intensity aerobic exercise, as well as two resistance training sessions each week (COSA 2018, World Cancer Research Fund, 2018). Exercise during cancer treatments has been widely studied and reported as a safe intervention for individuals with cancer (Cormie 2018). However, despite the clear clinical guidelines and safety reports, approximately 80% of women with BC do not meet these exercise recommendations and 23% reduce their usual activity level during cancer treatment (Gildea 2023). Systematic reviews suggest that even if supervised exercise programs successfully increase physical activity levels, these physical activity levels were maintained in only four out of ten trials (Weemaes et al., 2023). Women with BC commonly report that transitioning from supervised to self-managed exercise is one of the most significant barriers to maintaining physical activity (Ferri et al., 2021). Hence, there is a clear need to develop strategies to improve adherence to participation in exercise in this population.

Engaging in regular exercise during chemotherapy is arguably more challenging relative to other phases of the treatment trajectory due to common and debilitating physical side effects, such as fatigue, nausea and cancer related pain (Kirkham 2014). Such side effects from chemotherapy are the most commonly reported barrier to adherence to exercise during chemotherapy treatment for women with breast cancer (Kirkham 2014). Other cited barriers include inconvenient exercise locations, disease stage and poor baseline strength or fitness (Courneya 2008, Gildea 2023). Currently, as part of usual care, people known to the Breast Clinic at RPH are seen by a physiotherapist who provides education regarding the importance of exercise during their cancer treatment. Patients are provided with a pamphlet and encouraged to engage in appropriate off-site exercise groups. It is understood that uptake of exercise is suboptimal. This study will explore the effect of an experimental exercise program, known as the *SMART* program. This intervention has been co-designed, along with people who have BC, to overcome many of the known barriers to exercising during their cancer treatment. The *SMART* program will include individualised exercise prescription, monitoring of adherence, goal setting, strategies to optimise social support, action and coping planning and regular 'coaching' support to guide individuals through their exercise intervention. Importantly, this intervention will be available to people known to RPH, but who cannot access RPH due to transport problems and because they live outside Perth (i.e. rural and remote regions).

